#### CONSIDERATIONS IN PEDIATRIC PATIENTS

We estimate that 340 cases will be prospectively included from 17 participating centers during the 34-month follow-up.

Microbiology and immunology testing procedures will be similar to those in the adult cohort, adjusting blood collection volume to the maximum allowed for age and weight in pediatric patients.

Recent studies have suggested the involvement of an altered IL17 immune response in the context of invasive infections (CID 2019, PMID: 30165412), although it is most commonly described in the context of *S. aureus* of the skin and mucous membranes. Consequently, we propose to determine circulating IL-17A and Th17 (CD4+CXCR3-CCR6 +CCR4+ CD161+) levels at the time of blood culture sampling in the prospective cohort (Laboratorio 205, “Errores Innatos de Inmunidad”, Ibis; Laboratory 205, “Inborn Errors of Immunity”, Ibis).

#### **9. Quality control.**

All personal data necessary for the conduct of the study will be collected and processed in accordance with the provisions of Order SAS/3470/2009 on observational post-authorization studies for medicinal products for human use, Regulation (EU) 2016/679 of the European Parliament and of the Council of 27 April 2016, on the protection of natural persons with regard to the processing of personal data and on the free movement of such data, and repealing Directive 95 / 46 / EC (General Data Protection Regulation), the Spanish regulations in force on data protection, and Article 16.3 of Law 41/2002, of November 14, 2002, which regulates patient autonomy and the rights and obligations regarding clinical information and documentation.

#### **10. Limitations of the design, data sources and methods of analysis**

The primary objective has the limitation of not being a randomized study, but sets out to reflect ‘real-world’ patients, many of whom are not included in randomized trials. To minimize confounding and indication bias, we designed a propensity score matched-pair analysis. For the secondary objectives, we cannot predict the baseline MICs and mutations of the isolates, which may make it difficult to find a relationship with outcome variables if they are infrequent; nevertheless, a negative result would also be of interest.

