## 5. Expected sample size and basis for determination.

For the retrospective study (objectives 1-3) based on the ISAC database: we estimate that we will be able to analyze at least 1,800 cases of SAB that meet the inclusion criteria. For objective 4: we estimate prospective inclusion of 1000 cases from the 14 participating centers during 34 months of follow-up.

For objective 5: we estimate that 3 or 4 phenotypes will be identified, and therefore that 100 patients/isolate will be sufficient to provide 25-33 patients per phenotype, which will allow a reasonable number of cases for comparison of microbiological, genetic, endothelial and immunological parameters.

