## **8. Data analysis.**

ISAC Cohort: Objectives 1 and 2: Missing value analysis and imputation, if applicable, will be performed using standard techniques. To derive the phenotypes, a two-step cluster analysis with silhouette analysis will be performed on a randomly selected subcohort including two-thirds of the patients. The phenotypes will be represented as chord diagrams and heat maps. The distribution of phenotypes and characteristics will be validated on the other subcohort with one-third of the patients. Multivariate analysis (Cox or logistic regression) will be performed to control for the effects of antibiotic treatment and control of focus of infection on the association between the identified phenotypes and the outcome variable. Objective 3: A binary (if two phenotypes are obtained) or multinomial (if >2) logistic regression model will be used to predict the phenotypes obtained. A simplified probabilistic model of phenotype assignment will then be developed based on the final logistic regression model selected.

Prospective cohort: (Objective 4). Each patient with SAB will be assigned a phenotype that will be calculated on the basis of the simplified probabilistic model. Mortality rates (at 30 days and six months), persistent bacteremia and complicated bacteremia will be compared between the different types of phenotypes. Multivariate analyses (Cox or logistic regression) will be calculated to control for the effect of other covariates

(such as treatment administered or source control) on the association between identified phenotypes and outcome variables.

Study of genetic, immunological, biochemical and microbiological variables in representative patients with different phenotypes, randomly selected from the prospective cohort of HUVVM and HUVV cases (Objective 5):

Differences in frequencies or medians of the data for genetic virulence factors, biomarkers or immunological factors across the different phenotypes will be analyzed by the chi-square or Mann-Whitney U test and multivariate logistic regression models, taking into account possible confounding variables.

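### Objective 5 makes no provision for zero cells, so the confounder-adjusted odds ratio for a rare feature will often not be finite

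*Combined protocol and SAP*

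**What the plan says.** The substudy that the Methods call Objective 5 (secondary objective 4 in the list of objectives) takes 100 patients or isolates from two centres.

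- **Size.** Methods 5 states "we estimate that 3 or 4 phenotypes will be identified" and that "100 patients/isolate will be sufficient to provide 25-33 patients per phenotype". The justification is qualitative: "which will allow a reasonable number of cases for comparison of microbiological, genetic, endothelial and immunological parameters". No prevalence, effect size, significance level or power is given.
- **Analysis.** According to Methods 8, phenotype comparisons of each marker's frequency or median "will be analyzed by the chi-square or Mann-Whitney U test and multivariate logistic regression models, taking into account possible confounding variables". It names no exact, penalised or profile-likelihood method and no rule for empty or sparse cells. It does not say whether the adjusted tests are Wald or likelihood-ratio tests.
- **Data type.** The microbiological section derives resistance and virulence genes from sequencing, and the host-genetic section genotypes candidate variants. Many of these are yes/no features.
- **Frequency.** Methods 10 says that MICs and mutations are not known in advance, "which may make it difficult to find a relationship with outcome variables if they are infrequent". The statement is conditional and is about outcome variables. It offers no analytic response.

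**The concern.** Adjusted logistic regression is the only confounder-controlled analysis planned for Objective 5. Phenotypes are built from demographic and clinical characteristics, so a crude association between a gene and a phenotype leaves open whether the gene relates to the phenotype apart from those characteristics.

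In groups of 25-33, a feature carried by a few per cent of isolates will often be absent from one group by chance alone. A feature that really is concentrated in some phenotypes will be absent from another even more often. The maximum-likelihood fit then does not converge to a finite odds ratio. Software typically prints a very large coefficient with a far larger standard error and a p-value near 1.

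A report could thus show a clear crude result next to an adjusted p-value of about 1, with no prespecified way to read the pair. Any repair chosen after the zero cells are seen, such as merging phenotypes or dropping covariates, would be data-driven.

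**Working it through.** **Inputs from the plan.** 100 patients or isolates and 3 or 4 phenotypes (Methods 5). 100/4 = 25 and 100/3 = 33.3, which reproduces the stated 25-33.

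**Assumptions.** Feature prevalences, a two-sided 5% level and independent isolates. The plan gives none of these.

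**Step 1: chance of a zero cell at equal prevalence p.** For k groups of n: 1 - (1 - (1 - p)^n)^k.

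| p | 3 x 33 | 4 x 25 |
|---|---|---|
| 2% | 88% | 98% |
| 5% | 46% | 73% |
| 10% | 9% | 26% |
| 15% | 1.4% | 6.7% |

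For p = 5% and n = 25: 0.95^25 = 0.277, and 1 - 0.723^4 = 0.73. The 2% row includes features absent from every group, which no method can analyse. Without them it falls to 75% and 84%.

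Table S9 supplies one observed anchor. Methicillin resistance in the prospective cohort is 14.8%, 7.5% and 9.7% in phenotypes A, B and C. With 33 each, the zero-cell chances are 0.852^33 = 0.005, 0.925^33 = 0.076 and 0.903^33 = 0.035. At least one zero cell then has probability 1 - 0.995 x 0.924 x 0.965 = 0.11.

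**Step 2: non-finite odds ratio when prevalences differ (2% v 20%, two groups).**
- 33 each: 0.98^33 = 0.513 and 0.80^33 = 0.0006, so 1 - (1 - 0.513)(1 - 0.0006) = 0.51.
- 25 each: 0.98^25 = 0.603 and 0.80^25 = 0.004, so 1 - (1 - 0.603)(1 - 0.004) = 0.60.

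This is for the model with phenotype alone. Adding confounders cannot remove separation and can create more.

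**Step 3: what each method returns on a zero-cell table.**

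| Table | Pearson p | ML log-OR (SE) | Wald p | Firth OR | Firth p |
|---|---|---|---|---|---|
| 0/25 v 5/25 | 0.018 | 19.8 (8039) | 0.998 | 13.7 | 0.020 |
| 0/25 v 8/25 | 0.002 | 20.4 (8039) | 0.998 | 24.8 | 0.0015 |
| 0/33 v 8/33 | 0.003 | 20.1 (6997) | 0.998 | 22.3 | 0.0018 |

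The ML log-OR and SE are where the iterations were stopped; they are not estimates. In this two-group case Firth's estimate equals adding 0.5 to each cell. For 0/25 v 5/25: (5.5 x 25.5)/(0.5 x 20.5) = 13.7.

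**Step 4: power at 2% v 20%, by exact enumeration of two binomials.**

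| Test | 33 each | 25 each |
|---|---|---|
| Wald, ordinary ML | 14% | 8% |
| Firth penalised likelihood-ratio | 69% | 59% |
| Pearson chi-square (planned) | 74% | 59% |
| Ordinary likelihood-ratio | 77% | 67% |
| Fisher exact | 48% | 30% |

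With equal prevalences of 5% and 10%, Firth rejects in 2-3% and 4-5% of samples, Pearson chi-square in about 2-6% overall, and the ordinary likelihood-ratio test in 7-9%.

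**The case against.** A reader might infer that the clearest signals would be missed. The documents do not support that. Methods 8 plans the chi-square as well as the regression, and in the 2% v 20% case the chi-square has at least as much power as Firth. Setting Wald (14%) against Firth (69%) alone would exaggerate the loss.

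Three further objections have force:

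- **No Wald test is named.** A likelihood-ratio test from the same unpenalised model would detect these contrasts. That stands, but the test is somewhat liberal here and still gives no finite estimate.
- **Rare features are not predicted.** Methods 10 says only that frequencies are unknown and that rarity would cause difficulty, and it speaks of outcome variables. The gap therefore lies in the Objective 5 text of Methods 8, and nothing there says the candidate host variants are rare.
- **No hierarchy is set.** The plan does not say that the adjusted result overrides the crude one, or that a feature without a finite odds ratio would be discarded. Either would be conjecture.

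It may also be tempting to replace the chi-square with an exact test because expected counts will often be below 5. In the two-group case that cuts power from 74% to 48%, or from 59% to 30%, while the chi-square's error rate is already close to or below 5%. The calculations give no reason for that change.

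What remains is that the adjusted comparison has no method that works when a cell is empty.

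**Conclusion.** The point holds in a limited form. For features of low prevalence, the planned adjusted odds ratio will often be non-finite: 51% (33 each) or about 60% (25 each) of samples at 2% v 20%. Zero cells are common at an equal prevalence of 5% (46-73%) and much less so at 10% (9-26%) or above. The loss is the confounder-adjusted estimate, its interval and its Wald test. Strong crude contrasts remain detectable with the planned chi-square.

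The size depends on the assumed prevalences, and the power figures come from two-group models without covariates. That the regression is unpenalised is inferred from the absence of any named alternative. The importance is minor: this is a secondary substudy of 100 patients with no power claim, and the remedy is nearly free.

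**What to change.** In Methods 8, under Objective 5, state that adjusted models for binary isolate and host-genetic features will be fitted by Firth-penalised logistic regression, with penalised likelihood-ratio p-values and profile-likelihood confidence intervals. Keep the chi-square for crude comparisons. Keep the limitation sentence in Methods 10, because it remains true: at 2% prevalence about two of 100 isolates carry the feature, and penalisation does not create information.

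The cost is one sentence and standard software, with no extra data. The downside is that estimates are shrunk slightly towards no effect. Very rare features will stay uninformative, with wide intervals.

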**ETHICAL CONSIDERATIONS / PROTECTION OF PARTICIPATING SUBJECTS:****1. Risk/benefit assessment for research subjects.**

This study carries no risk as it is non-interventional and involves no additional or different treatment than would have been given if the patient had not participated in the study. There will be no financial benefit to patients participating in the study.

**2. Considerations relating to information to participating subjects and informed consent.**

A report from the Andalusian Biomedical Research Ethics Coordinating Committee is required.

This protocol complies with the principles of the Declaration of Helsinki for research projects involving human subjects.

Participants (approximately 100) selected for the microbiological (clonality, genome sequencing), biochemical and immunological analyses aimed at elucidating pathophysiological and genetic mechanisms underlying the phenotypes (Objective 5) will be informed of the nature of the study and its objectives, and will consent to participate by signing the informed consent form as a prerequisite for participation in the study.

**3. Data confidentiality.**

All personal data necessary for the development of the study will be collected and processed in accordance with the provisions of Regulation (EU) 2016/679 of the European Parliament and of the Council of 27 April 2016 on the protection of individuals with regard to the processing of personal data and on the free movement of such data, and repealing Directive 95/46/EC (General Data Protection Regulation), the current Spanish legislation on data protection, and Article 16. 3 of Law 41/2002, of November 14, 2002, which regulates patient autonomy and the rights and obligations regarding clinical information and documentation.

**4. Interference with the prescribing habits of the physician .**

This study is entirely observational and will not interfere with prescribing habits, since patients will be included in the study once their physician (independent of the research staff participating in the study) has prescribed the treatment he/she considered appropriate according to usual clinical practice.

**MANAGEMENT AND REPORTING OF ADVERSE REACTIONS.**

As previously indicated, this study is observational, and the type of antibiotic treatment administered will be only one of the explanatory variables that will be collected and recorded in order to achieve the proposed objectives outlined above. Therefore, IT IS NOT CONSIDERED AN OBSERVATIONAL STUDY WITH

MEDICINES, AS IT DOES NOT FALL UNDER ANY OF THE SUPPOSITIONS GIVEN IN ARTICLE 2 OF ROYAL DECREE 957/2020, OF NOVEMBER 3, REGULATING OBSERVATIONAL STUDIES ON MEDICINES FOR HUMAN USE.

#### **PLANS FOR THE DISSEMINATION OF THE RESULTS.**

The first publication will be once the inclusion period has ended and the database used by the participating centers is closed. Partial publication of results will not be allowed.

Publication of results will be in scientific journals or those available to the public, with mention of the CEIm that evaluated the study.

#### **RESOURCES FOR THE CONDUCT OF THE STUDY AND TASK ALLOCATION; METHOD OF SUPPLY OF THE MEDICATION; FUNDING.**

There is no financial compensation for patients or investigators, nor are there any undeclared sources of funding that might represent a conflict of interest for the results.

The Project has received funding from the Instituto de Salud Carlos III (Carlos III Institute of Health), with file number P121/018901 and the Fondo Europeo de Desarrollo Regional (FEDER) from the Ministerio de Hacienda y Función Pública, Gobierno de España. Has the necessary resources to carry it out.

**PROTOCOL MODIFICATIONS.**

This version is version 1.0 and has not been previously modified.

**PRACTICAL CONSIDERATIONS:****1. Follow-up and interim reports.**

As has been stated above, this is not an observational study with medicines for human use. Royal Decree 957/2020, of November 3, which regulates observational studies with medicines for human use is not therefore applicable. Nevertheless, the Sponsor will send the follow-up reports required by the CEIm (the Ethics Committee for Research with medicines) for approval.

**2. Dissemination of the results**

The results of this study will be communicated at different international, national and regional conferences specialized in Infectious Diseases and/or clinical microbiology.

They will also be submitted for publication in international journals with impact factor.

**ANNEXES (not included in the protocol):**

**Annex 1: Data collection sheet.**

**Annex 2: Commitment of the coordinating investigator.**

**Annex 3: Agreement / Decision of the 1° CEI (Ethics Committee for Research) that evaluated the study.**

**Annex 4: Subject information sheet (only for patients selected for objective 5).**

**Annex 6: Informed consent form (only for patients selected for objective 5).**

**Annex 7: Financial report.**
